### 12.4 Laboratory Assessments

All screening and on-study samples will be processed and sent to the laboratory. The laboratory will be responsible for performing the assays. Biochemical examination (complete blood count, renal function, liver function and 25-OH-vitamin D), blood pressure and observation of abnormal symptoms/signs based on standardized patient report forms performs at

baseline and 12, 24, and 36 months (Table 1). Serum osteocalcin or urine deoxypyridinoline is as a marker predicting hip fracture in elderly women (Szulc and Chapuy et al., 1996). Serum 25-OH-vitamin D, osteocalcin, 17 $\beta$ -estradiol and urine deoxypyridinoline should be obtained in the morning after an overnight fast and be delivered to the laboratory for measurements using commercial kits.

### 12.5 Uterus Endometrial Thickness Monitoring

We will monitor uterus endometrial thickness using transvaginal ultrasound (Siemens Medical Solutions Systems, Issaquah, WA, USA). Endometrial thickness will be measured at the thickest portion of the endometrium and be included both endometrial layers. The sensitivity of detecting endometrial abnormalities is 92% and for detecting cancer is 96% when an endometrial thickness of 5 mm is used as the upper limit of the normal value (Smith-Bindman and Kerlikowske et al., 1998). During each clinical visit, abnormalities should be evaluated and documented, and follow-up medical care should be provided as needed.

## 13. SAFETY DATA REPORTING

### 13.1 Adverse Events Definitions

An adverse event is defined as “any untoward medical occurrence in a patient or clinical investigation subject administered a pharmaceutical product and that does not necessarily have a causal relationship with this treatment.”

This definition of adverse events is broadened in this study to include any such occurrence (eg, sign or symptom) or worsening of a pre-existing medical condition from the time that a subject has signed informed consent to the time of initiation of BSYJF or placebo. Worsening indicates that the pre-existing medical condition (e.g. migraine headaches and gout) has increased in severity, frequency, or duration of the condition or an association with significantly worse outcomes.

The investigator is responsible for reviewing laboratory test results and determining whether an abnormal value in an individual study subject represents a change from values before the study. In addition, interventions for pretreatment conditions or medical procedures that were planned before study enrollment are not considered adverse events. Abnormal laboratory findings without clinical significance (based on the investigator's judgment) should not

be recorded as adverse events; however, laboratory value changes requiring therapy or adjustment in prior therapy are considered adverse events.

### 13.2 Serious Adverse Events

A SAE is defined as an adverse event that:

- is life threatening or fatal;
- is a congenital defect;
- requires hospitalization;
- results in persistent or significant disability/incapacity;
- major bleeding (e.g. gastro-intestinal or intracerebral);
- end-stage renal disease requiring renal replacement therapy;
- any other major health conditions/events.

A hospitalization meeting the regulatory definition for “serious” is any inpatient hospital admission that includes a minimum of an overnight stay in a health care facility. Any adverse event that does not meet one of the definitions of serious (eg, emergency room visit, or requires urgent investigation) may be considered by the investigator to meet the “other significant medical hazard” criterion for classification as a SAE.

### 13.3 Adverse Event Collection and Reporting

Any adverse events occurring after the first dose of study medication will be recorded in the subjects’ records and on the CRFs. Information about the occurrence of any adverse events will be sought at all scheduled visits. The investigator is responsible for ensuring that all adverse events observed by the investigator or reported by subjects if SAE occurs. The SAE is reported within 24 hours to the coordinator by completing a Serious Adverse Event Form (Appendix D). In addition, the investigator should ensure that all regulatory requirements are completed.

The following adverse event attributes must be assigned by investigator: diagnosis, signs or syndrome(s) (if known); dates of onset; severity; assessment of relatedness to BSYJF/placebo and action taken. The investigator may be asked to provide follow-up information, discharge summaries, and extracts from medical records or CRFs.

A subject may voluntarily withdraw from treatment due to what she perceives as an intolerable adverse event. If either of these situations arises, the subject

should be strongly encouraged to undergo an end-of-study assessment and be under medical supervision until symptoms cease or the condition becomes stable. Documentation of all such SAEs will be retained in medical records.

#### 13.4 Safety Monitoring

Monitoring visits will occur on at least 2 occasions in the first year and on at least one occasion each year thereafter. Sites will provide 3-monthly progress reports with information on participant, adverse events, and any protocol deviations. PI will review the reports from the site monitoring visits and the site progress reports every year.

The report will include:

- A list and summarization of adverse events by age and other characteristics
- Whether adverse event rates are consistent with pre-study assumptions;
- Reason for dropouts;
- Whether all participants met entry criteria;
- Whether continuation of the study is justified on the basis that additional data are needed to accomplish the stated aims of the study;
- Conditions whereby the study might be terminated prematurely.

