## 9. DRUG ADMINISTRATION

### 9.1 Packaging and Formulation

All the participants will be received daily calcium carbonate 300 mg as the basic treatment. The participants will be orally given BSYJF capsules or placebo capsules (3 capsules per time, 3 times per day) for 36 months. All the capsules should package in identical plastic bottles (100 capsules per bottle) and subsequently delivered to the participants every 3 month at each clinical visit. All the participants will be told to take the capsules with element calcium before meal. The quality control for screening and verification of adherence to the protocol will perform by the supervisor. BSYJF/placebo will be manufactured, packaged, and distributed by Shuguang Hospital.

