## **12. Measurements** (This section has been amended. Please refer to the information in “Amendment” section.)

During the study, every effort should be made to keep subjects on the study schedule of procedures (Table 1). These measurements should be performed at baseline and 12, 24, and 36 months. The study window is ranging from -7 to 7 days.

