| ECG                              |           | √        | √         | √         | √         |                     |                     |                      |
| B-ultrasound                     |           | √        | √         | √         | √         |                     |                     |                      |
| DDIPA                            |           | √        | √         | √         | √         | √                   | √                   | √                    |
| Adverse events                   |           |          | √         | √         | √         |                     |                     |                      |
| Others                           |           |          |           |           |           |                     |                     |                      |
| Drug dispensing                  |           | √        | √         | √         |           |                     |                     |                      |
| Drug return                      |           |          | √         | √         | √         |                     |                     |                      |
| Combined disease and Medications | √         |          | √         | √         | √         |                     |                     |                      |

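### Table 1 and Section 12.4 schedule adverse event collection once a year, while Section 9.1 has 3-monthly visits and Section 13.4 needs 3-monthly adverse event reports; the plan does not say which visits count

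*Supplement*

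**What the plan says.** All references are to the protocol, with Table 1 taken from Amendment 2 (version 1.2).

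- **Table 1, Schedule of Assessments (updated).** The visits are screening, baseline, months 12, 24 and 36, and three extension years. The row "Adverse events" is ticked at months 12, 24 and 36 only. No 3-monthly visit is shown.
- **Section 12.** Sites are told to keep subjects on Table 1, and "These measurements should be performed at baseline and 12, 24, and 36 months".
- **Section 12.4.** Abnormal symptoms and signs are taken from standardized patient report forms at baseline and months 12, 24 and 36, with a reference to Table 1.
- **Section 9.1.** Capsules are "subsequently delivered to the participants every 3 month at each clinical visit".
- **Section 13.3.** "Information about the occurrence of any adverse events will be sought at all scheduled visits". Scheduled visits are not defined. The section also says "Any adverse events occurring after the first dose of study medication will be recorded in the subjects’ records and on the CRFs", and for serious events: "The SAE is reported within 24 hours to the coordinator".
- **Section 13.4.** "Sites will provide 3-monthly progress reports with information on participant, adverse events, and any protocol deviations".

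The nature, frequency and severity of adverse events and their relationship to treatment is a named secondary endpoint (Section 15.2 as amended). Adverse events are compared by chi-square test (Section 16.3 as amended).

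**The concern.** Two sites could each follow the protocol in good faith and collect this endpoint on different timetables, one asking every quarter and the other once a year.

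On the annual timetable, the events at risk are non-serious ones that a woman does not volunteer. She may be asked about them many months later. Section 13.3 requires the investigator to assign an onset date, severity and relatedness, and each is harder to assign after a long delay. Mild and moderate events are the likeliest to be forgotten or misdated. Under-recording in both arms would make an excess on BSYJF harder to see.

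Section 13.4 also uses the reports to judge whether event rates match pre-study assumptions and whether continuing is justified. A quarter in which few or no women were asked can look reassuring for the wrong reason.

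**Working it through.** The plan states no figure on this point, so there is none to reproduce. The check is a count under each reading, followed by an illustration.

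**1. Per-woman count.** Inputs: 36 months of treatment (Section 5.1 as amended), a 3-month reporting interval (Section 13.4) and three adverse event ticks (Table 1).
- Quarterly points: 36 / 3 = 12.
- If Table 1 is the full list of visits: asked at 3 of 12 points, so 9 / 12 = 75% have no questioning. Recall is up to 12 months.
- If Section 13.3 covers the Section 9.1 visits: asked at 12 of 12 points. Recall is up to 3 months.

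**2. Pooled site reports, Table 1 reading only.** Section 13.4 reports come from sites, so they pool women at different stages. The accrual length is not stated. Section 17.5 says start dates depend on accrual, and the synopsis gives a five-year intervention window (January 2000 to December 2004) for 36 months of treatment, so up to about 24 months of staggered entry would fit. Assume steady entry over A months, with every open window containing at least one visit.
- Reporting windows: (36 + A) / 3.
- Windows with an annual visit: A, for A up to 12 (A / 3 windows after each of months 12, 24 and 36). For A = 24 the visits run without a gap from month 12 to month 60, so only the first four windows are empty.

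| Accrual (assumed) | Windows | With a visit | Empty | Share empty |
|---|---|---|---|---|
| 3 months | 13 | 3 | 10 | 77% |
| 6 months | 14 | 6 | 8 | 57% |
| 9 months | 15 | 9 | 6 | 40% |
| 12 months | 16 | 12 | 4 | 25% |
| 24 months | 20 | 16 | 4 | 20% |

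A simulation with 70 women at a site (an equal split, assumed) gave the same shares. Staggered entry fills the reports but shortens no woman's recall.

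**3. Illustration of what longer recall could cost.** The documents give no recall rate and no adverse event risk, so both are assumed. With questioning every T months and a recall half-life of h months, the fraction of events captured is (1 − 2^(−T/h)) × h / (T ln 2). For h = 6:
- T = 12: 0.75 × 6 / (12 × 0.693) = 0.541.
- T = 3: 0.293 × 6 / (3 × 0.693) = 0.845.

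Take assumed true risks of 20% and 40% and 70 women per arm, with the chi-square test at two-sided 5% and power by exact enumeration. Full capture gives 0.747. Multiplying both risks by the captured fraction gives:

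| Half-life (assumed) | Captured, annual | Captured, 3-monthly | Power, annual | Power, 3-monthly |
|---|---|---|---|---|
| 3 months | 0.338 | 0.721 | 0.264 | 0.556 |
| 6 months | 0.541 | 0.845 | 0.415 | 0.645 |
| 12 months | 0.721 | 0.918 | 0.556 | 0.695 |

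The gap shrinks under other models. At a half-life of 6 months, if events recur within a woman (Poisson, same risks of ever having one), power is 0.515 against 0.686. If half of events are found without recall, it is 0.592 against 0.698. The loss is therefore 0.230, 0.171 or 0.105, depending on the model.

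**The case against.** The strongest reply is that the text can already be read as quarterly collection. Section 13.3 seeks events at all scheduled visits, Section 9.1 describes a clinical visit every 3 months, and Section 13.4 expects quarterly adverse event data. Nothing says that Table 1 lists every visit. It plainly omits the visits of Section 9.1, so a missing tick is weak evidence that nobody asks. This stands to the extent that annual questioning cannot be called the plan's settled intention. It does not remove the conflict. Section 12.4 separately places the symptom and sign forms at the annual visits, Section 12 directs sites to Table 1, and Amendment 2 reissued the table without the 3-monthly visits.

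A reader might also infer that three in four site reports contain no newly sought events. The documents do not support this: 9 of 12 is a count per woman, and the share of pooled reports depends on an accrual period that is not given.

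Nor do the documents support the inference that nothing is known between annual visits. All events after the first dose must be recorded, volunteered events can be reported at any time, and serious events go to the coordinator within 24 hours.

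Finally, the power figures rest on assumed recall rates and assumed risks, and the plan sets no power target for adverse events. That objection stands in full.

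**Conclusion.** The inconsistency is real and remains in version 1.2: annual collection in Table 1 and Section 12.4, 3-monthly visits in Section 9.1, 3-monthly reports in Section 13.4, and an undefined term in Section 13.3 that could settle the matter either way.

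The firm part of its size is the per-woman contrast of 3 against 12 points of questioning, and up to 12 against up to 3 months of recall. It depends only on which reading a site adopts. The share of empty site reports (20% to 77% over the accrual periods tried) applies only on the Table 1 reading. Longer recall lowers power at all three half-lives tried, but the amount is illustrative and should not be quoted as a property of this trial. It would be wrong to conclude that every woman must recall a full year.

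This is a clarification worth making, because it concerns a named secondary endpoint and is cheap to settle. It does not undermine the trial.

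**What to change.** Reconcile Table 1 and Sections 9.1, 12.4, 13.3 and 13.4:

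- Add the existing 3-monthly visits of Section 9.1 to Table 1 and tick adverse events at each, with onset date, severity and relatedness recorded.
- State in Section 13.3 that all scheduled visits include these 3-monthly visits.
- Align Section 12.4, so that the annual timing of laboratory tests and report forms is not read as the only time events are sought.

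Each Section 13.4 report would then rest on events sought in that quarter. No visit beyond those in Section 9.1 and no new test is needed. The cost is added table columns and a sentence or two of text, a few more minutes at each 3-monthly visit, and more adverse event pages to enter.

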#### 14. DROPOUT

If any investigator encounters a participant dropout, such as moving away from proximity of the site, incompatible with the intervention (withdrawal), and discontinued the intervention over 3 months. The decision of participant dropout will be reported to the required PI.

Participants will continue to be followed with their permissions if the study intervention is discontinued at the site. These participants will be followed up annually for 36 months for clinical outcomes and adverse events of (1) death from any cause; (2) hospitalization event. We will evaluate compliance by counting the residual at each visit (practical dose/dose application × 100%). Good compliance means the drug actually taken equals 80% to 120 % of the required dosage.

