#### With:

A fall is defined as any event that led to an unplanned, unexpected contact with a supporting surface. Falls resulting from pathologic fracture, major trauma or facial trauma, and/or unavoidable hazards such as transient ischemic attacks, chair collapsing or cerebrovascular accidents will be excluded. A faller is defined as the participants sustained at least one fall or more. Information about new falls while on study will be documented using form, included the date of fall and related-injury. The number of falls is accumulated. **The cumulative incidence of fallers will be calculated as the total number of participants with first fall at each time point divided by the number of participants at risk.** A copy of radiograph confirming the fracture will be obtained.

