#### With:

#### **Primary endpoint:**

**Primary endpoint is the number of falls at 36 months.**

## Section: 15.2 Secondary Endpoints

Replace:

- (1) Change from month baseline at month 36 in osteocalcin;
- (2) Change from month baseline at month 36 in deoxypyridinoline;
- (3) Changes from baseline at month 36 in estradiol;
- (4) Change from month baseline at month 36 in endometrial thickness;
- (5) Nature, frequency and severity of adverse events and their relationship to treatment.

With:

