| Endpoints                  | 
Endpoints are to be evaluated for BSYJF versus placebo.
 
Primary endpoint:
 
 
1. Number of falls at month 36.
 
 
Secondary endpoints:
 
 
1. Change from month baseline at month 36 in femoral neck BMD;
 
2. Change from month baseline at month 36 in lean mass of left thigh;
 
3. Change from month baseline at month 36 in TUG test;
 
4. Change from month baseline at month 36 in biomarkers of bone turnover (osteocalcin and deoxypyridinoline).
 
5. Change from month baseline at month 36 in endometrial thickness;
 
6. Change from month baseline at month 36 in estradiol;
 
7. Nature, frequency and severity of adverse events and their relationship to treatment.
 
 
Additional endpoint:
 
8. Number of falls at the end of 10 years extension follow-up.
 |
| Statistical considerations | 
All the analyses will use all randomly assigned patients under ITT principle. For patients missing data after the baseline, the LOCF approach use to analyze the longitudinal data. The number of falls at month 36 and adverse events will perform by chi-square test. Kaplan–Meier analysis will be calculated in order to demonstrate differences in number of fallers over time. The time to first fall will be analyzed using a Cox regression
                                                                                                                                                                                                                                                                                                                                                                                                                                                                                                                 |

|  |                                                                                                                                                                                                                                                                                                                                                                                                                                                                                                    |

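### The plan does not require falls, its only primary endpoint, to be recorded after a woman stops treatment, and the chi-square test takes no account of the missing time

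*Supplement*

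**What the plan says.** - **Primary endpoint.** Amendment 1 (replacement text for Section 15.1) leaves one: "Primary endpoint is the number of falls at 36 months". Amendment 2 keeps it. The amended Section 12.3 makes it a running total, "The number of falls is accumulated", and on collection says: "Information about new falls while on study will be documented using form".
- **Stopping treatment.** Section 14 includes among dropouts a woman who has "discontinued the intervention over 3 months". It then says: "Participants will continue to be followed with their permissions if the study intervention is discontinued at the site". The follow-up is described as "followed up annually for 36 months for clinical outcomes and adverse events of (1) death from any cause; (2) hospitalization event". Neither amendment changes Section 14. Amendment 2 adds an instruction to record falls, but only for the 10-year extension.
- **Analysis.** The Amendment 2 synopsis says: "All the analyses will use all randomly assigned patients under ITT principle". Its one rule for missing data is: "For patients missing data after the baseline, the LOCF approach use to analyze the longitudinal data". Falls at month 36 are tested by chi-square, two-sided at 5%. Kaplan–Meier and Cox analyses of time to first fall are also planned.
- **Expected dropout.** Section 11 allows for 20%, with 70 women recruited per group and a placebo fall incidence of 19%.

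**The concern.** An intention-to-treat comparison needs the outcome of every randomized woman to month 36, on treatment or off. The plan keeps all women in the denominator and keeps annual contact with those who stop, but the items named for those contacts leave out the primary endpoint. If Section 14 is followed as written, falls after discontinuation are lost.

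What happens next depends on how the gap is filled. If LOCF is applied to a cumulative count, or the count is simply taken as last recorded, a woman who stops is treated as never falling again. If LOCF does not apply to falls, the chi-square has no missing-data rule at all. A plain chi-square takes no account of time observed, so an arm in which more women stop, or stop earlier, shows fewer falls for that reason alone. Falls not recorded at the time cannot be reliably recovered later.

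**Working it through.** **Plan's own figure.** 55 per group with 20% dropout: 55 / (1 − 0.20) = 68.75, so 69. The plan states 70, which agrees within rounding. The 20% is therefore the plan's working figure for dropout.

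**Amount of missing time.** 20% of 140 is 28 women. If stopping times are uniform over three years, each loses 1.5 years on average: 28 × 1.5 = 42 of 140 × 3 = 420 person-years, or 10%. If all stopped at the start, it would be 84 of 420, or 20%.

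**Assumptions for the illustration.** The 19% in Section 11 is read as an annual probability of falling, and the hypothesised halving gives 9.5%. The chi-square is taken to compare proportions of fallers. Stopping times are uniform over 36 months and unrelated to fall risk. The dropout splits by arm are mine, since the documents give only the overall 20%.

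**Fallers when the last recorded count stands.** With annual probability a and dropout proportion d:

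- by month 36: P = 1 − (1 − a)³
- average up to a uniform stopping time: M = 1 − P / (3 × (−ln(1 − a)))
- recorded fallers: (1 − d) × P + d × M

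For a = 0.19: P = 1 − 0.81³ = 0.4686 and M = 1 − 0.4686/0.6322 = 0.2588. With no drug effect the false difference is (P − M) × (difference in dropout) = 0.2098 × (difference in dropout). The ratio of expected fall counts is (1 − d_BSYJF/2) / (1 − d_placebo/2).

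| Dropout, placebo v BSYJF | Recorded fallers, placebo v BSYJF | False difference | Count ratio |
|---|---|---|---|
| 20% v 20% | 42.7% v 42.7% | 0 points | 1.00 |
| 15% v 25% | 43.7% v 41.6% | 2.1 points | 0.875/0.925 = 0.95 |
| 10% v 30% | 44.8% v 40.6% | 4.2 points | 0.85/0.95 = 0.89 |

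**Effect on the error rate.** With 70 per group, the standard error of the difference is √(2 × 0.4266 × 0.5734 / 70) = 0.0836. A shift of 0.0210 is 0.25 standard errors, giving a two-sided rejection rate of Φ(−1.71) + Φ(−2.21) = about 5.7% instead of 5%. A shift of 0.0420 is 0.50 standard errors, giving Φ(−1.46) + Φ(−2.46) = about 7.9%.

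**With the hypothesised effect and 20% dropout in each arm.** For a = 0.095: P = 0.2588 and M = 0.1358.

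| Scenario | Fallers, placebo v BSYJF | Difference | Risk ratio | Two-sided power, n = 70 |
|---|---|---|---|---|
| Last recorded count stands | 42.7% v 23.4% | 19.2 points | 0.55 | 68% |
| Falls followed, effect persists after stopping | 46.9% v 25.9% | 21.0 points | 0.55 | 74% |
| Falls followed, effect ends at stopping | 46.9% v 28.1% | 18.8 points | 0.60 | 63% |

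In the last row, a BSYJF woman who stops has an average three-year risk of 0.3695, so 0.8 × 0.2588 + 0.2 × 0.3695 = 0.281. Against the second row, the recorded counts understate the difference and cost power. Against the third, they overstate the effect and gain power.

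**The case against.** The strongest reply is that the documents do not shut falls out. The reference to clinical outcomes in Section 14 can be read apart from the two numbered items, and falls are the trial's main clinical outcome. Section 12.3 ties recording to being on study, not to being on treatment. Section 13.3 encourages an end-of-study assessment after withdrawal for an adverse event. This stands in part: a reader might infer that the plan stops fall recording at discontinuation, and the text does not say so. But the list in Section 14 names two items, and no passage requires falls after stopping within the 36 months. Site staff following that list would have no instruction to ask about them.

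Three stronger readings are not supported:

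- **That LOCF is laid down for the fall count.** The rule is attached to longitudinal data, and the measures taken at four visits are its natural object. Its use on falls is an inference. The alternative is that falls have no rule, which leaves the primary test undefined for these women.
- **That every fall analysis is affected in the same way.** Kaplan–Meier and Cox analyses ordinarily censor at last contact. Scoring unobserved time as fall-free concerns the chi-square. The other two would still lack falls after stopping. All randomized women also remain in the analysis set, so the fault is incomplete outcome data, not exclusion.
- **That power is lost.** A fall from 74% to 68% appears only if the effect persists after stopping. If it ends at stopping, full follow-up gives about 63%, below the 68%.

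It is also fair to say that the bias is modest at moderate imbalance, and that the documents give no reason to expect a particular split by arm.

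**Conclusion.** The concern holds as a gap in outcome collection joined to an unsuitable or absent missing-data rule for the primary endpoint. As written, the plan does not secure falls after discontinuation, and the chi-square would then approximate a comparison of falls while on treatment under an intention-to-treat label. On the assumptions above and with no drug effect, the false difference is nil with equal dropout, 2.1 points at 15% v 25% and 4.2 points at 10% v 30%, with rejection rates of about 5.7% and 7.9%. The direction follows whichever arm loses more follow-up. With equal dropout and a real effect, the direction depends on whether the effect outlasts treatment, which the documents do not settle. The actual size cannot be taken from the documents. The point still matters because it touches the only primary endpoint, the plan itself expects 20% dropout, and the data must be collected at the time.

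**What to change.** In Section 14, list falls and fractures, recorded on the Appendix C form, among the outcomes collected to month 36 whatever the treatment status, at the annual contacts already planned and with the woman's permission.

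In Section 16.3:

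- State that LOCF is not used for falls.
- Analyse observed falls over observed follow-up, using a count model with log follow-up time as offset.
- State that the Kaplan–Meier and Cox analyses censor at last contact.
- Add one sensitivity analysis in which unobserved time after dropout on BSYJF is given the placebo fall rate.

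The cost is a line in Section 14, a short paragraph in Section 16.3 and slightly more data collection at existing contacts. There are limits: falls in women off treatment would rest on annual recall, and women who move away or refuse contact would still have missing data. The sensitivity analysis is there for them.

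### Sections 13.3 and 14 conflict on which adverse events are recorded after treatment stops, and the chi-square over all randomised women ignores observation time, so unequal stopping could distort the safety comparison

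*Supplement*

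**What the plan says.** Section 14 (Dropout) covers women who stop treatment: "Participants will continue to be followed with their permissions if the study intervention is discontinued at the site". They are then "followed up annually for 36 months for clinical outcomes and adverse events of (1) death from any cause; (2) hospitalization event". No other adverse event is named, and neither amendment changes this section.

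Section 13.3 gives the general collection rule: "Information about the occurrence of any adverse events will be sought at all scheduled visits". It does not limit this to women still on treatment. It also foresees stopping for intolerance: "A subject may voluntarily withdraw from treatment due to what she perceives as an intolerable adverse event". Such a woman "should be strongly encouraged to undergo an end-of-study assessment and be under medical supervision until symptoms cease or the condition becomes stable".

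The latest analysis text is the synopsis in Amendment 2. It sets the population, "All the analyses will use all randomly assigned patients under ITT principle", and the test, "The number of falls at month 36 and adverse events will perform by chi-square test". The missing-data rule is "For patients missing data after the baseline, the LOCF approach use to analyze the longitudinal data". Nothing says whether women or events are counted, over what period a woman is at risk of a recorded event, or what is done when that period is cut short. Adverse events, including their type, frequency and severity, remain a secondary endpoint. Section 11 allows for 20% drop-out, as one overall figure.

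**The concern.** Under Section 14, a woman who stops at month 4 stays in the denominator for 36 months. After month 4 she can add a death or a hospitalization but no other adverse event. A chi-square on all randomised women treats her as fully observed. If one arm has more stopping, the two arms are observed for different lengths of time and the test does not know it.

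Under Section 13.3 she would still be asked about any event at each scheduled visit, and the problem largely goes away for women who agree to be followed. Two sites could read the sections differently, and data not collected after stopping may not be recoverable later. Safety is named in the trial's title, so the plan should not leave this open.

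**Working it through.** **1. The plan's own figure on stopping.** Section 11: 55 per group at 20% drop-out gives 55/(1 − 0.20) = 68.75, so 69; the plan recruits 70. The figure reproduces to within one woman. If that 20% all stop treatment, at times spread evenly over 3 years, 14 women per arm lose 1.5 years each on average: 14 × 1.5 = 21 of 70 × 3 = 210 woman-years. About 10% of ordinary adverse event observation is then lost in each arm.

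**2. Inputs the documents do not give.** There is no adverse event rate and no split of stopping by arm or by reason. All that follows is illustration: constant event rate *h* per woman-year, stop times uniform over 36 months, and non-serious events recorded only up to stopping (the Section 14 reading).

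**3. Extra stopping not caused by an adverse event.** With share *d* stopping, the recorded proportion with at least one event is

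(1 − d)(1 − e^(−3h)) + d[1 − (1 − e^(−3h))/(3h)].

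Example, h = 0.1: 1 − e^(−0.3) = 0.2592, and 1 − 0.2592/0.3 = 0.1361. At d = 0.30: 0.7 × 0.2592 + 0.3 × 0.1361 = 22.2%. At d = 0.10: 0.9 × 0.2592 + 0.1 × 0.1361 = 24.7%.

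With the same true rate in both arms and 30% v 10% stopping:

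| h per year | 30% stop | 10% stop | Difference | True hazard ratio that would be hidden |
|---|---|---|---|---|
| 0.1 | 22.2% | 24.7% | 2.5 points | 1.13 |
| 0.2 | 39.0% | 43.1% | 4.1 points | 1.15 |
| 0.4 | 61.4% | 67.1% | 5.6 points | 1.18 |

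The last column is the hazard ratio at which the two recorded proportions become equal. At 25% v 15% stopping the differences are 1.2 to 2.8 points and the hidden ratios 1.06 to 1.09. With equal stopping the difference is zero.

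On 70 women per arm, 2.5 to 5.6 points is about 2 to 4 women. The standard error of the difference is about 7 to 8 points.

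**4. Extra stopping caused by a recorded adverse event, by-woman count.** Let 10% of each arm stop for other reasons, and let a further share *a* of the active arm stop because of an event, which is recorded. Each of those women is a case under either collection rule. The recorded and the full-collection differences are then both a × e^(−3h). At a = 0.20 and h = 0.3 this is 0.20 × 0.4066 = 8.1 points both ways. A simulation of 2,000,000 women per arm gave +8.1 recorded and +8.1 with full collection, and agreement to 0.1 point at every rate tried (0.1, 0.3 and 0.6).

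**5. Same stopping, number of events per woman.** Each extra stop adds one event and loses 1.5 years on average, so the recorded excess is a(1 − 1.5h) against a true excess of a. At a = 0.20:

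- h = 0.3: 0.20 × 0.55 = +0.11 recorded v +0.20 true.
- h = 0.6: 0.20 × 0.10 = +0.02 recorded v +0.20 true.

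The excess shrinks but does not reverse at any rate tried. The formula would change sign only above 1/1.5 = 0.67 events per woman-year, outside that range.

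**6. Event types.** A woman who stops because of one event is no longer observed for a different one. For that second type, if it arises independently of the reason for stopping, her stopping acts as in step 3.

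**The case against.** A reader might infer that the arm with more intolerance will look safer than it is. The documents do not support that. A woman who stops for an intolerable event already has an event on her record under Section 13.3, and later silence cannot remove her from a count of women with any event. Step 4 shows no bias there. In a variant where stopping for other reasons acts independently in both arms, an arm with 20% extra intolerance stops still shows +14.1, +10.6 and +5.8 points at 0.1, 0.2 and 0.4 events per year, against +14.8, +11.0 and +6.0 with full collection. It plainly looks worse. The 2.5 to 5.6 points of step 3 assume stopping unrelated to the events counted, so they must not be quoted for intolerance.

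A reader might also infer that women who stop are certainly no longer asked about ordinary events. Section 13.3 has no on-treatment limit, and the annual contacts line up with the month 12, 24 and 36 visits at which Table 1 schedules adverse events. That objection stands in part: this is a conflict between sections, not a clear end to collection. But Section 14 is the specific rule for these women and it lists two events; if Section 13.3 were meant to govern, the list would serve no purpose. Supervision until symptoms settle covers the event that led to withdrawal, not later or different ones.

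It is also fair that the step 3 effect is smaller than its standard error and needs a stopping imbalance for which the documents give no evidence, and that simple proportions are an ordinary safety summary.

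**Conclusion.** The concern holds in a limited form. The plan does not settle which adverse events are recorded after treatment stops, what the chi-square counts, or over what time. If Section 14 governs and stopping differs by arm, event counts and later or different event types are under-recorded in the arm with more stopping. The any-event proportion is lowered only by extra stopping that is not caused by an adverse event: about 2.5 to 5.6 points at 30% v 10%, and 1.2 to 2.8 points at 25% v 15%, given constant rates of 0.1 to 0.4 per year, uniform stop times and independence from events. It is zero with equal stopping, and the by-woman any-event comparison is unaffected when a recorded event caused the stopping. The bias is conditional and moderate, on a secondary endpoint. It is still worth correcting, because the change is small and the information may be lost for good otherwise.

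**What to change.** 1. **Sections 13.3 and 14.** Reconcile them so that all adverse events, not only death and hospitalization, are recorded to month 36 at the annual contacts already planned for women who stop and agree to be followed.
2. **Section 16.3 and the synopsis.** State that the unit is women with at least one event, overall and by event type. Keep the simple proportions, and add the rate per person-year under adverse event observation, with a rate ratio and 95% CI.

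The cost is a sentence or two in each place and a few more questions at a contact that already exists; no visit is added. The rate analysis has limits: it assumes a roughly constant hazard, and it does not by itself remove bias from informative stopping. The first change matters more, because it secures the data.
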